### Entomology

Standard CDC light traps will be used to estimate the potential exposure to malaria mosquitoes in the bedrooms of study children in 110 novel design houses and their nearest comparison house from October 2021 to December 2023. The study area will be divided into seven geographically separated clusters, six each with 16 Star homes and 16 control houses and one with 14 Star homes and 14 control houses. Each cluster will further be divided into four sub-clusters, each with eight houses: four Star homes and four nearest neighbours’ control houses. The light traps will be suspended 1 m from the ground at the foot end of a bed where a study child is. Collections will be made from one cluster each week, with a different sub-cluster sampled on four consecutive nights each week, Monday night to Thursday night. At the end of the week, all houses will be sampled in each cluster (i.e. 32 houses). The sequence in which clusters will be visited was randomly determined. The clusters will be visited in the same sequence throughout the study period, so that each cluster will be visited in a 7-week cycle. Malaria vectors collected in the study houses will be counted and compared between the intervention and control houses and then packed in the Eppendorf tubes containing silica gel and submitted to the laboratory, for further analyses. The mosquitoes will be identified by microscopy and the numbers of *An. gambiae* s.l., *An. funestus* s.l., and other species will be recorded. The presence of sporozoites will be identified using an enzyme-linked immunosorbent assay [24], and *An. gambiae* s.l. females, typed by PCR [25].

The abundance and species of domestic flies will be assessed using baited traps installed in the cooking area of selected households, outdoors, and in latrines to assess the difference in fly densities between the two study arms. The traps will be positioned on the kitchen floor, in the corner furthest from the main door. Research assistants will collect the captured flies each evening.

### Social science

A mixed-method approach will be deployed for the assessment of acceptance and the use of each component of the novel design house (i.e. kitchen, storage area, bedroom, latrine, water collection facility). Data will be collected using focus group discussions (FGDs), in-depth interviews (IDIs), and a structured questionnaire-based survey at the beginning of the study and after 1 to 2 years. In-depth interviews will be conducted with approximately 18 selected heads of the households as well as selected members of the community (community leaders, health workers, religious leaders, etc.) to get their perspectives of the new house designs (design elements, construction materials, aesthetic appearance, etc.) and use of the house. FGDs will be conducted with a group of eight to 10 participants including respondents from both study arms and other selected members of the community to explore the community’s perception of the novel design houses. Approximately 10 FGDs will be conducted with approximately a total of 100 participants taking part in the discussions. The construction costs of novel design houses will be estimated and used to assess incremental costs and cost-effectiveness of the interventions.

### Architecture and environment

Data loggers will be used to record environmental data. The data will be recorded in intervals throughout the follow-up period and downloaded weekly or monthly intervals depending on the storage capacity of the device. Rainfall, temperature, relative humidity, and wind speed and direction will be recorded using an automatic weather station placed in the centre of the study area. Indoor temperature, relative humidity, and carbon dioxide concentrations will be recorded in the bedrooms of study homes in eight Star homes and eight neighbouring traditional study homes each week. PM2.5 will be monitored in the kitchens and bedrooms of study and control houses. Readings will be made every 30 min for three consecutive nights. GasLab data loggers will be positioned at the foot end of the study child’s, 1 m above the floor. Aerosol dispersion will be studied using computational fluid dynamics to digitally model the aerosol movements in space. The model will be informed by the environmental data and further qualified by targeted on-site registrations.

### Timeline for the star homes project

The timeline for the star homes project is presented in Fig. 3.

**Fig. 3 Fig3:**
[figure not shown]
Estimated timeline for the Star Homes Project. Project activities started in 2018 and will be completed in 2025

### Mitigation of bias and confounding

The intervention—a novel house design—makes it impossible to conduct a blinded trial. Researchers and village residents are aware of who lives in an intervention and a control house. The awareness of the intervention allocation can lead to differences in the detection of diseases and hence introduce bias. The study team aware of this risk will take all possible steps to prevent differences in data capture between the study arms. Observer bias will be minimized wherever feasible.

Stratified randomization by village will reduce the likelihood of imbalances due to differences in geographic characteristics between the study groups. In addition, data on potential confounding factors will be collected and corrected for in the analysis. Laboratory technicians will be blinded to the identity and intervention status of the subjects. Collector bias will be reduced by using standard light traps and fly traps which do not rely on the ability of the fieldworker to collect specimens. Trap catches will be examined by a different person blinded to the trap location.

The study participants can only benefit from the house design intervention if they make use of the new houses and sleep upstairs. Children moving between houses and not regularly sleeping upstairs in study houses will be identified during weekly interviews with the household head or guardian and censored in the analysis.

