### Intervention

The intervention consists of a novel house design. Its structure is informed by pilot studies in Magoda, Tanzania [14]. The critical components are an elevation of the sleeping area by constructing double-storey buildings and the use of shade net as cladding to optimize airflow while minimizing the entry of insects (Fig. 1). To assure timeliness in construction and identical physical characteristics of all new houses, a light gauge steel structure was chosen by the architects. The building site was selected by the house owners in discussion with the architects to address the requirements of the house owners and optimize shade throughout the day. The raised concrete foundation serves as the ground floor and can be easily cleaned. The ground floor includes a protected lockable storage area to reduce rodent infestation and to provide a feeling of security. Each of the 3 doors comes with a spring-powered closing mechanism to minimize the time that the doors stay open. The frequency of opening and closing of the door will be recorded by data loggers via sensors. The ground floor cooking area is screened to improve airflow and reduce the entry of flies. The kitchen includes a chimney to direct the flow of smoke away from the building. Rainwater is harvested in roof gutters, which drain into 2000-l PVC water tanks. The outdoor latrines are constructed within a 10-m radius of the building, using a light gauge steel system with a fly-proof, ventilated septic tank. Each house comes with a solar power system which provides electricity for light and mobile phone charging. The new homes are designed to minimize energy consumption through reduced use of concrete and optimized airflow and ventilation. By our estimates, a novel design house uses 37% less embodied carbon, 41% less embodied energy, and 70% less concrete than a more traditional African home design of similar size [18].

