### Study endpoints

#### Primary endpoints

Incidence of malaria will be calculated in children under 13 years participating in the study for 3 years, using the number of detected cases as the numerator and the period contributed by each child residing in the study area as the denominator. These data will be analysed and used to determine the relative risk of malaria among children living in the novel design houses compared with those living in traditional sub-Saharan African homes.

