### Analytical plan

#### Incidence of malaria, respiratory tract infections, and diarrhoea diseases

Protective efficacy against clinical malaria, pneumonia, and diarrhoea diseases will be assessed by comparing incidence rates between the two study arms adopting an intention-to-treat analysis. Children within each household will be monitored using active and passive case detection throughout the study period. After treatment for malaria, the child will not be considered at risk for the following four weeks and this period will be censored. History of travel and nights spent away from the designated household will be captured during weekly surveillance visits and time at risk will be censored for such periods. Initial unadjusted analyses will be based on the comparison of the incidence rates between the two arms. Formal analyses will use a mixed effects Poisson model to test the difference in incidence rate between the two arms allowing for the repeated measurements within a house, a village and the effect of year using of confidence intervals that account for the highest level of clustering [28]. With multiple control and intervention houses within each village, the “intervention*village” interaction will also be quantified. Possible confounders such as age of child, gender, ethnicity, and rainfall will be tested using the mixed effects model. A mixed effects negative binomial model will be considered in case of overdispersion in the mixed effects Poisson model. A comparison of time to infection (both first and repeat) will be examined using a survival analysis approach. Initial analyses will be based on Kaplan-Meier curves with further adjustment for confounders performed using a Cox regression model.

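### The incidence analysis is labelled intention-to-treat, yet children who do not regularly sleep upstairs are censored, a condition that in practice can be failed only in the novel-house arm

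*Protocol article*

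**What the plan says.** Two sections of the protocol article decide which child-time enters the incidence comparison.

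- **Analytical plan, incidence of malaria, respiratory tract infections and diarrhoea.** Protective efficacy is assessed by "comparing incidence rates between the two study arms adopting an intention-to-treat analysis". The same paragraph removes four weeks after each malaria treatment and adds that "nights spent away from the designated household will be captured during weekly surveillance visits and time at risk will be censored for such periods". Both exclusions are worded without reference to arm.
- **Mitigation of bias and confounding.** Participants "can only benefit from the house design intervention if they make use of the new houses and sleep upstairs". The next sentence begins: "Children moving between houses and not regularly sleeping upstairs in study houses will be identified during weekly interviews". From its second condition to its end it reads: "not regularly sleeping upstairs in study houses will be identified during weekly interviews with the household head or guardian and censored in the analysis".

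On the houses, the Intervention section says: "The critical components are an elevation of the sleeping area by constructing double-storey buildings". The Abstract and Background describe traditional rural houses as usually single-level, and the household eligibility criteria require mud walls, a thatched roof and a dirt floor.

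On use, the Discussion says that some families are sceptical about the new houses, that children may sleep with neighbours or relatives, and that this dilutes protection. No rate of non-use is given. The article describes no separate per-protocol or as-used analysis to which the upstairs rule could belong.

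**The concern.** Intention-to-treat means that children are analysed in the arm their household drew in the lottery, whatever they then do. A rule that censors children because they do not use the intervention is the opposite, and here it is justified by adherence. Both statements cannot govern the same analysis.

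The upstairs part of the rule also has no counterpart among controls. Applied literally to single-level homes it would censor almost every control child, so in practice it will be applied to the 110 novel houses and not to the 440 traditional ones. Families who use the house and families who do not may differ in malaria risk. If so, removing the non-users from one arm only undoes the balance that the lottery created. Sleeping place is also reported by guardians, to staff who know the allocation, at the same weekly visits that detect fever.

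At stake are the meaning and the validity of the primary rate ratio. It would describe children who use the house, while being reported as the effect of being allocated one.

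**Working it through.** The plan gives no figure to reproduce on this point. The check sets the two rules side by side and then shows what one-arm censoring can do.

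**Inputs from the article.** 110 novel and 440 traditional households; about 3 children per household (330/110 and 1320/440) followed for 3 years, so about 9 child-years per household; 0.10 malaria episodes per child-year in controls and 0.07 under the planned 30% reduction; coefficient of variation 0.25; 5% significance level, taken here as two-sided.

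**Assumed inputs, not in the article.** q is the share of novel-arm time that is censored. h is the incidence in censored children relative to retained children.

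**1. Bias when the house has no effect.** Let retained children have incidence r. By randomisation the control arm holds the same mix of would-be users and non-users, so its incidence is r(1 − q + qh). The novel arm after censoring shows r. Hence

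apparent rate ratio = 1 / (1 − q + qh)

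| q | h | 1 − q + qh | Apparent rate ratio |
|---|---|---|---|
| 0.05 | 1.5 | 1.025 | 0.98 |
| 0.10 | 2 | 1.10 | 0.91 |
| 0.20 | 2 | 1.20 | 0.83 |
| 0.20 | 1 | 1.00 | 1.00 |
| 0.20 | 0.67 | 0.934 | 1.07 |

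**2. False-positive rate.** This was simulated with 5000 trials per scenario: 110 against 440 households, 9 child-years each, overall rate 0.10, gamma household variation with CV 0.25, non-use set per household, and a two-sided 5% test of the log ratio of mean household rates. With no true effect and censoring in the novel arm only, the test rejects in about 11% of trials at q = 0.1, h = 2 and about 27% at q = 0.2, h = 2. At q = 0.2, h = 1 it rejects in 4.9%. With all allocated time kept, rejection stays between 4.8% and 5.7% in every scenario run.

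**3. The quantity estimated when the house works.** Suppose the rate ratio is 0.70 among users, 20% of novel-arm time is non-use without benefit, and non-use is unrelated to risk (h = 1). The effect of allocation is

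0.8 × 0.70 + 0.2 × 1 = 0.76

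The censored analysis still reports 0.70.

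**4. Power cost of keeping everyone.** For novel-arm rate r1 in c households and control rate r0 = 0.10 in 440,

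variance = (r1/9 + 0.25²·r1²)/c + (0.10/9 + 0.25²·0.10²)/440, and power = Φ((r0 − r1)/SE − 1.96).

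- r1 = 0.07, c = 110: SE = 0.01001, 0.03/SE = 3.00, power about 85%.
- r1 = 0.076 (rate ratio 0.76), c = 110: SE = 0.01033, 0.024/SE = 2.32, power about 64%.
- r1 = 0.07, c = 88 (20% of novel households censored): SE = 0.01089, 0.03/SE = 2.76, power about 79%.

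So 85% assumes full use. With 20% non-use, the choice is between about 79% for the as-used contrast and about 64% for the allocation contrast.

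**The case against.** The strongest reply has four parts.

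**The rule may be narrower than it looks.** Its subject is children who move between houses *and* do not regularly sleep upstairs. If both conditions must hold, the target is children sleeping elsewhere. Moving between houses can happen in either arm, and nights away from the designated household are censored by a rule worded for both arms. This stands in part: a novel-house child sleeping at a relative's home has a counterpart among controls. The clearly one-sided remainder is time in the designated house spent sleeping downstairs, and the article does not say how common that is. But even on the narrow reading the upstairs condition helps decide who is censored, and it has no meaning in a single-level home.

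**One-sidedness is an inference.** That is correct. It rests on the house designs, and traditional homes are called single-level only as the usual case. The inference is strong, because the alternative reading would empty the control arm.

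**Non-use may be small or harmless.** The new house often replaced the old one, and community engagement aims at full use. Eligibility criteria narrow differences in housing, and age, gender and ethnicity are to be examined in the model. These points reduce the likely bias without removing the contradiction.

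**The size is assumed.** This is also correct. A reader might infer that censoring could manufacture the whole planned 30% reduction, since q = 0.40 with h = 2 gives 1/1.4 = 0.71. The article does not support treating that corner as likely. At q = 0.1 or 0.2, h would have to be 5.3 or 3.1 to reach 0.70.

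Two further inferences should not be drawn. The denominator under Primary endpoints, "the period contributed by each child residing in the study area as the denominator", might look like a third, conflicting rule, but it can be read as a general definition that the analytical plan then refines. It might also seem that an infection acquired on a night away is counted while its exposure time is dropped. The article does not say how such cases are attributed, and an analysis plan commonly settles this.

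**Conclusion.** The contradiction is explicit and concerns the primary endpoint: the analytical plan declares intention-to-treat, and the bias section censors for non-use. Because the article states both rules, this is not a detail left to an unseen analysis plan. Followed as written, the upstairs condition would make the comparison partly as-used.

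The illustrated bias under no effect runs from negligible (0.98) to material (0.83), depending on assumed values of q and h. It is absent at h = 1 and reverses below 1. The mismatch in what is estimated does not need h to differ from 1: if the house works, 20% non-use separates 0.70 from 0.76. The finding is therefore that the rule can bias the primary rate ratio and mislabels it. The documents do not show that it will do so, or by how much.

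**What to change.** - In the primary analysis, keep all children and their time under surveillance in the arm allocated by lottery, whether or not they sleep upstairs. Apply one time-at-risk rule identically in both arms.
- Use sleeping-place censoring only in a secondary analysis labelled as-used.
- Reword the bias section and the analytical plan so that they state the same rule.
- Travel and nights-away censoring is worded for both arms but also depends on behaviour after allocation. At the least, report the censored time by arm and add a sensitivity analysis without this censoring.

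No new data are needed, since travel, nights away and household use are already to be recorded. The cost is statistical. The primary effect may be diluted and power reduced: about 85% at a rate ratio of 0.70 against about 64% at 0.76, under the inputs shown above. That dilution is part of the effect of allocating the house, which is what an intention-to-treat analysis estimates.

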To reduce malaria and enteric and respiratory tract infections and to improve the indoor climate and safety of our latest design (Fig. 1), the following critical structural components are included:Building orientated to provide optimal shading throughout the day to keep the house cooler at night (→ indoor climate)Lightweight and durable roof with partially closed eaves to reduce the entry of malaria vectors (→ malaria, indoor climate)Facade and openings screened to reduce insect entry while assuring airflow (→ malaria, diarrhoeal diseases, indoor climate)Raised concrete ground floor which can be easily cleaned and increases hygiene and reduces the risk of enteric and soil-transmitted infections (→ diarrhoeal diseases)A screened indoor cooking area with the means to remove smoke to reduce indoor pollution (→ respiratory infections)A protected lockable storage area to reduce rodent infestations and provide a feeling of security (→ safety)Sleeping areas with bednets raised to the first floor improving airflow and comfort while reducing mosquito density (→ malaria, indoor climate)A water harvesting system which allows the collection of rainwater from the roof, filtering, and covered storage (→ diarrhoeal diseases)An outdoor fly-proof latrine (→ diarrhoeal diseases)Solar power providing electric light at night (→ safety)

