Although unique and without precedent our study has several limitations. Firstly, it is impossible to blind the study subjects and field researchers from the intervention. We will try to address this handicap by conscientiously assuring that the same procedures are applied to all participants and that those analysing samples in the laboratory are blinded to the source of the sample. Secondly, since our primary outcome is disease incidence, the capture of all disease episodes is of critical importance. This will be achieved through a combination of active cases detection supported by passive case detection in all health facilities in the study catchment area. It is possible to miss disease episodes if the guardians of study participants fail to inform the research assistants and seek either no healthcare at all or seek healthcare outside the recognized system. Building rapport and ultimately gaining the trust of the families living in study houses will be the key strategy for the capture of all disease episodes. Thirdly, some families are sceptical about using the novel houses. Community sensitization and engagement will continue throughout the trial period to ensure full compliance. A multipronged community engagement programme is underway addressing the fears of using the houses to facilitate the understanding between the study communities and the researchers. Finally, and perhaps most importantly, the interventions can only work if the study participants sleep and more broadly live in their assigned homes. If children assigned to novel design homes sleep in the homes of neighbours or relatives, they cannot be protected by the novel home design. Data will hence be collected on household use to assess how often children sleep in the novel design houses. This type of dilution of protection may be most intense for respiratory tract infections and diarrhoea where study participants can be infected at any time of the day including while attending schools without a safe water supply, and where sanitation and ventilation have not been improved. As falciparum malaria is predominantly transmitted by endophagic and endophilic vectors in sub-Saharan Africa, most of the transmission occurs at night at home. Hence the impact on malaria transmission of novel home designs may be least diluted. Potential protection against respiratory tract infections and diarrhoea could be reduced through infections acquired outside the home.

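### Censoring children who do not regularly sleep upstairs conflicts with the declared intention-to-treat analysis, and the upstairs condition can be failed only in the novel-house arm

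*Protocol article*

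**What the plan says.** Three parts of the protocol article decide which child-time enters the comparison.

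- **Analytical plan, incidence of malaria, respiratory infections and diarrhoea.** Efficacy is assessed by "comparing incidence rates between the two study arms adopting an intention-to-treat analysis". Time is removed for four weeks after malaria treatment and for absence: "nights spent away from the designated household will be captured during weekly surveillance visits and time at risk will be censored for such periods". Sleeping upstairs is not mentioned.
- **Primary endpoints.** The denominator is each child's period of residence in the study area, again with no upstairs condition.
- **Mitigation of bias and confounding.** Participants "can only benefit from the house design intervention if they make use of the new houses and sleep upstairs". Children who move between houses and are "not regularly sleeping upstairs in study houses will be identified during weekly interviews with the household head or guardian and censored in the analysis". The analysis meant is not named.

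The Intervention section describes a double-storey house: "Sleeping areas with bednets raised to the first floor improving airflow and comfort while reducing mosquito density". The Background describes traditional rural houses as single-level, and household eligibility requires a traditional mud-walled, thatched, dirt-floored house. The Discussion expects uneven uptake: "some families are sceptical about using the novel houses".

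**The concern.** An intention-to-treat analysis keeps randomised children in their allocated arm whether or not they use what they were allocated. A rule that censors child-time because the upper floor was not slept in is an adherence restriction, and the reason given for it (benefit only with use) confirms this.

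It also cannot act symmetrically. Applied literally to both arms it would censor every control child, so in practice the upstairs condition operates only in novel houses. Users of the upper floor would then be compared with all controls. Use is chosen after allocation, in an open-label trial, and is established by interview. If users and non-users differ in background malaria risk, randomisation no longer protects the rate ratio. If they do not differ, the estimate describes efficacy among users but carries an intention-to-treat label.

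The rule is not limited to malaria. The Intervention section lists the raised floor, water harvesting and latrine against diarrhoea, and the smoke-removing kitchen against respiratory infection. None of these depends on where the child sleeps.

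**Working it through.** The plan prints no figure for non-use, so there is none to reproduce. Its sample-size figure does not enter this point and does not change with the fix.

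**Inputs from the protocol.** Control rate 0.10 episodes per child-year, household coefficient of variation (CV) 0.25 and a 5% test (Sample size calculations; two-sided is assumed); 110 and 440 households (Study design); 1650/550 = 3 children per household over 3 years, so 9 child-years per household (Abstract).

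**Assumed inputs.** q = share of novel-arm child-time censored by the rule; k = background risk in that time relative to users' time. The protocol gives neither.

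**Ratio when the house has no effect.** Let users' rate be r. The novel-arm average is r[(1−q) + qk], and randomisation gives controls the same average. Censoring leaves r in the novel arm only, so

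ratio = r / (r[(1−q) + qk]) = 1/[(1−q) + qk].

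**Error rate.** With control rate 0.10 and novel rate λ = 0.10 × ratio, the variance of the rate difference is approximately

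[λ/(9(1−q)) + 0.25²λ²]/110 + [0.10/9 + 0.25² × 0.10²]/440.

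For q = 0.2, k = 1.5:

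- ratio = 1/(0.8 + 0.3) = 0.909, so λ = 0.0909
- novel-arm term = (0.01263 + 0.00052)/110 = 0.0001195
- control term = (0.01111 + 0.00063)/440 = 0.0000267
- standard error = √0.0001462 = 0.0121
- standardised shift = 0.0091/0.0121 = 0.75
- chance of falsely declaring benefit = Φ(0.75 − 1.96), about 11%, against a nominal 2.5%
- adding the other tail, the two-sided error is about 12% against 5%

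| q | k | ratio with no true effect | two-sided error |
|---|---|---|---|
| 0.1 | 1.5 | 0.95 | 7% |
| 0.2 | 1.25 | 0.95 | 7% |
| 0.2 | 1.5 | 0.91 | 12% |
| 0.2 | 2 | 0.83 | 30% |
| 0.3 | 1.5 | 0.87 | 18% |
| 0.3 | 2 | 0.77 | 49% |

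If non-users are at lower risk the bias reverses: q = 0.2, k = 0.5 gives 1/(0.8 + 0.1) = 1.11. With k = 1 the ratio is 1 for any q.

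These figures are approximate. They ignore the village effect and the covariates in the planned model, and they treat non-use as spread evenly across households.

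**The case against.** **The sentence has an opening condition.** It concerns children who move between houses *and* do not regularly sleep upstairs. A reader might infer that a child at home every night, but sleeping downstairs, will certainly be censored. That follows only if the two conditions describe separate groups. If both must hold, fewer children are affected and the rule partly overlaps the nights-away rule, which can apply in both arms. This stands and narrows the point. It does not remove it: the upstairs condition is still one that only a novel-arm child can fail, and the wording leaves both readings open.

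**The analysis is not named.** A reader might infer that the primary comparison is bound to be adherence-selected. The documents do not go that far. The Analytical plan lists its own exclusions without this one, and the Discussion treats sleeping elsewhere as dilution of protection, which fits keeping such children in. What can be said is that the article speaks of the analysis without qualification and assigns the rule to no secondary analysis, so the passages conflict.

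**Size and direction are unknown.** This stands in full. Nothing in the documents supports a particular q or k, or a claim that the bias favours the novel house.

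**Partial benefit downstairs.** A reader might also infer a fixed overstatement. If users have a ratio of 0.70 and a 20% non-using share has 1.0, intention-to-treat gives 0.8 × 0.70 + 0.2 × 1.0 = 0.76, so 30% efficacy would be reported in place of 24%. This assumes no protection without sleeping upstairs. The protocol undercuts that assumption: screened single-storey pilot houses had 70% less mosquito entry (Background), and the screened facade and partially closed eaves are listed against malaria (Intervention). With an assumed 0.80 in non-users, intention-to-treat would be 0.8 × 0.70 + 0.2 × 0.80 = 0.72, close to 0.70.

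**Conclusion.** The contradiction is real and should be resolved before analysis. The upstairs rule cannot coexist with an intention-to-treat comparison or with a denominator based only on residence. It can operate in one arm only, and it depends on behaviour that the protocol itself expects to vary. This is a rule the article states, not a detail left to a statistical analysis plan.

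Following it could bias the primary rate ratio by an amount and in a direction the documents do not determine. Under no true effect, assumed values of q from 0.1 to 0.3 and k from 1.25 to 2 give ratios from 0.98 (q = 0.1, k = 1.25) down to 0.77; k below 1 gives ratios above 1. If k = 1 there is no null bias, and the fault is that efficacy among users is reported as intention-to-treat. The conclusion that the passages conflict does not depend on any of these values, or on how the sentence's conjunction is read.

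**What to change.** Reconcile the sections on mitigation of bias, primary endpoints and the incidence analysis:

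1. Remove the upstairs-sleeping censoring from the primary analysis. Keep all cases and child-time of children in their allocated arm, wherever in the home they sleep.
2. Apply any remaining at-risk rules identically in both arms, and describe them accurately. Censoring nights away can also depart from intention-to-treat, so the label should match what is done.
3. Use the weekly record of sleeping place to report the share of novel-arm child-time not slept upstairs.
4. Put the upstairs-use restriction in a labelled per-protocol or sensitivity analysis, and state whether moving between houses and not sleeping upstairs must both hold.

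An analysis using allocation as an instrument for sleeping upstairs is not advised. The screened facade and eaves can affect malaria by other routes, so its exclusion assumption would be doubtful.

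The cost is a few sentences in the protocol and, where one exists, the statistical analysis plan, with no new data collection. The downside is that the primary estimate may be less favourable if non-use is common.
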